### Overview

Musculoskeletal pain patients will be offered participation in this study until at least 342 patients have been enrolled in baseline assessment and 105 patients have been included into our randomized controlled proof-of-concept study. All 105 patients enrolled in the study will undergo detailed phenotyping before and after intervention, which, together with the response/non-response data from the RCT, will serve to improve the allocation algorithm for future studies. All patients eligible will be randomly assigned 1:1 to a personalized or non-personalized treatment arm (Fig. 1). Personalization is achieved by a targeted allocation either to a therapy focused on emotional distress, a therapy focused on dysfunctional behaviours and maladaptive learning or allocation to a minimal intervention group where adaptive responses to pain will be registered. After baseline assessments (Fig. 1, T_0_) for relevant pathomechanisms, each patient included in the trial will receive either 12 weekly sessions of cluster-matching therapy (intervention arms)—where patients are allocated personalized (i.e. according to their individual pain mechanism)—or non-cluster-matching therapy (control arms) —where they are allocated non-personalized (i.e. randomly assigned between the other two interventions). After the last session, all procedures included in the baseline assessment will be performed as a posttreatment evaluation (Fig. 1, T_1_). Furthermore, a 3-month follow-up by means of telephone interview and questionnaire package will be implemented for patients taking part in the intervention study (Fig. 1, T_2_). At T_2_, the maintenance of the effects on pain and pain-related impairments will be assessed. In order to guarantee a correct evaluation of our primary outcomes in pain change, we will include an extended psychological assessment (details on outcomes are given below).

**Fig. 1 Fig1:**
[figure not shown]
Intervention scheme/trial flow. Note: the same treatment interventions are applied in personalized as well as in non-personalized interventional study arms. However, the arms differ in the assignment to the respective treatment modules: While in the personalized assignment arms patients with high level of emotional distress receive an emotional distress-tailored intervention (EDDT), patients with high avoidance/maladaptive-learning behaviour receive an extinction/retraining-tailored treatment intervention (PERT) and patients with neutral risk profile receive a low-level diary intervention (EMDI), patients in the non-personalized arm receive a non-personalized intervention (i.e. patients with a high level of emotional distress receive either extinction/retraining-tailored or a low-level-tailored intervention, but not the emotional distress-tailored treatment). CMSP, chronic musculoskeletal pain; PERT, Pain Extinction and Retraining-Tailored Intervention; EDDT, Emotional distress desensitization and reprocessing-tailored intervention; EMDI, Ecological Momentary-tailored Low-Level Diary Intervention

### Sample

The inclusion and exclusion criteria are chosen to ensure good representativeness and to cover the heterogeneity of different musculoskeletal pain conditions and diagnoses.

*Key inclusion criteria*: CMSP >3 months as symptom of (1) non-specific chronic back pain, (2) osteoarthritis, (3) fibromyalgia syndrome or (4) rheumatoid arthritis. Symptoms must be present for at least 3 months to ensure clinically relevant chronicity; the ability to see and use a mobile telephone (incl. with visual aids), age ≥18 years (no upper age limit) and ability to provide informed consent.

The *key exclusion criteria* will contain insufficient or unclear treatment of the underlying disease (according to the practitioner’s judgement), application for retirement/pension pending, on-going psychotherapy, severe, pharmaceutically treated acute life-threatening physical comorbidity or physical comorbidity which is incompatible with participation in the study according to the practitioner’s judgement, severe mental disorder (inability to consent, suicidality, psychosis spectrum disorders), neurological comorbidity (epilepsy, traumatic brain injury, seizures, multiple sclerosis, neurodegenerative diseases) and pregnancy. Participants will be excluded from the MRI assessment, if they have implants or metal parts in their body, which are not compatible with 3T MRI, or diseases which prevent lying still for 60 min. Clinical evaluation will be carried out by study physicians with experience in the diagnosis and management of chronic pain conditions. All patients will undergo a clinical evaluation by the Heidelberg Study Center for Clinical Pain Research within the Department of General Internal Medicine and Psychosomatics of Heidelberg University Hospital [30].

Participants of the CMSP group will be recruited through our tertiary pain clinic at the University Hospital Heidelberg, the affiliated academic teaching hospital of the University of Heidelberg in Baden-Baden as well as the Central Institute of Mental Health in Mannheim. Should the recruitment rate prove to be insufficient, recruitment will be extended to cooperating general and specialist medical practices in the Rhein-Neckar area. All prospective participants will be screened before inclusion in the study. Screening data will be confirmed by a study physician specifically trained in the assessment of chronic pain conditions. CMSP patients will be entered into the trial until the necessary sample size is reached.

During the planning phase of the study, we involved patient representatives of patients with CMSP. Further, members of relevant patient groups were invited to an initial focus group to ensure patient-friendly study procedures and to reduce the patient burden at all stages. In addition, all participants will be asked systematically about their experiences and impressions during the study and results will be discussed together with patient representatives at regular meetings. For the communication of the results to patients, we will organize a patient forum after the completion of the study.

### Treatment personalization

With our pilot study, we aim to prepare a multi-centre randomized controlled trial (planned RCT) to assess the feasibility and safety of a mechanism-based personalized assessment and treatment approach for CMSP patients across disorders. To further improve the personalized allocation algorithm for the planned RCT, a comprehensive characterization of the study participants will be performed with dynamic quantitative-sensory testing paradigms, immunological and neuroendocrine assessments, psychological questionnaire assessments, longitudinal data collection in everyday life (EMA, ECG and activity sensors) and neuroimaging (fMRI) pre- and post-treatment.

As this pilot study compares a personalized treatment allocation based on patient characteristics with a non-personalized treatment allocation, the same treatment interventions are applied in both study arms. However, arms differ in the assignment to the respective treatment modules. In the personalized assignment arm, patients with high level of emotional distress receive an emotional distress-tailored intervention (EDDT: Emotional Distress Desensitization-tailored treatment), patients with high avoidance/maladaptive-learning behaviour receive an exposure/extinction-tailored treatment intervention (PERT: Pain Extinction and Retraining-Tailored Intervention) and patients with neutral risk profile receive a low-level smartphone-based intervention (EMDI: Ecological Momentary-tailored Low-Level Diary Intervention). For every intervention, a special standard operation procedure (SOP) protocol is written regarding the 12-week design and special psychological/pain characteristics of the patient groups. Patients in the non-personalized arm receive a non-personalized intervention allocation (e.g. patients with a high level of emotional stress receive either exposure/extinction-tailored or a low-level smartphone-based intervention, but not the emotional stress-tailored treatment). For this study, matching to the subtypes will be based on a cluster analysis of the West Haven-Yale Multidimensional Pain Inventory (MPI) as well as the age and gender of participants, which have been identified as significant predictors of MPI clusters in previous research. Cluster status of individual participants will be identified by using soft k-means clustering of previous data collected from CMSP patients by the study teams. Using this data, clusters were identified, and the most likely cluster status for participants in the current study will be determined by an automated script implemented in an electronic data collection tool (REDCap) using a random-forest decision algorithm using the established clustering algorithm. Based on this algorithm, participants in the intervention arm will be assigned to the intervention that best fits according to their cluster, while patients in the control arm will be randomly assigned to one of the interventions that do not fit their cluster.

### Interventions

The individual interventions consist of 12 weekly face-to-face sessions (EDDT, PERT), or a minimal intervention condition in which smartphone-based diary queries are monitored daily over a period of 12 weeks (EMDI). The efficacy and safety for all three treatment modules have been demonstrated in previous studies, yet their superiority in outcomes depending on patient cluster has not been formally addressed. During the trial, patients are encouraged not to change their existing therapies over the course of the therapy. All additional treatments will be recorded regularly. In order to ensure that therapy protocols are appropriate and that therapists learn to follow these protocols in early stages of the study, a subsample of pilot participants will be invited to take part in the interventions without being part of evaluation of the personalized treatment allocation algorithm to aid the quality assurance of interventions.

#### Emotional distress desensitization and reprocessing (EDDT) intervention

EDDT is a stress-reducing intervention that combines the use of well-established trauma intervention elements (including imaginal exposure and cognitive and self-control techniques) and the use of specific EMDR elements such as bilateral sensory stimulation (e.g. left–right eye movements or bilateral hand-tapping induced by the therapist’s fingers) and the dual focus of attention principle. With the dual focus of attention principle, patients simultaneously focus on distressing memories and an external bilateral sensory stimulus. This procedure is suggested to facilitate information processing of emotionally distressing memories (e.g. traumatic events or pain sensations) and thereby cause a decreasing or even an elimination of the emotional distress related to these memories. Recent studies have shown that the dual application of bilateral sensory stimulation is highly efficient in triggering the inhibitory effects of the thalamus on the amygdala [31]. This strategy is increasingly being used to treat patients with chronic pain and its efficacy in pain treatments has been shown in several randomized controlled trials [22, 32]. Promising results have been reported especially for chronic musculoskeletal disorders, including back pain [33] and inflammatory joint pain [34]. The treatment protocol for this study is based on a standardized manual [21] and the possible targets for processing will encompass disturbing memories, current pain perceptions and pain-related fears and cognitions, and anticipated future painful situations together with the associated cognitions, emotions and bodily sensations. Participants who are allocated to the intervention group will receive a manualized and 12-session outpatient psychotherapeutic EDDT intervention (weekly session for 100min).

#### Pain Extinction and Retraining-tailored (PERT) intervention

PERT is a structured cognitive-behavioural derived intervention that focuses on retraining and alterations of maladaptive brain responses and includes elements such as activity increase, reduction of compensatory behaviours, medication management, altering social interactions, training of pleasant events and improving sensory discrimination. The treatment is based on an extension of a standardized manual [35] and consists of 12 weekly 100-min sessions led by two psychologists and is conducted in groups of 5–6 patients. To ensure a good patient-therapist relationship, all patients will have two individual sessions with the therapist prior to the group therapy. The group therapy includes video feedback of expressions of pain as well as training of pain-incompatible behaviours, increase of work-related and social activities and medication management. Patients are encouraged to participate in role plays to reduce dysfunctional pain behaviour and promote healthy behavioural responses. To increase the transfer of the treatment effects from the clinic to everyday life of the patients, the training also includes several sessions together with their spouses. Spouses will be fully informed and consented just as study participants. In previous studies, we could show that PERT interventions are superior to multimodal pain interventions and that maladaptive brain activation patterns can be altered by such interventions [15, 36–39]. In a study that is currently under review (Thieme, Kleinböhl et al., submitted), we analysed post hoc to what extent a matching of PERT to patients who are highly dysfunctional compared to those who are characterized by traumatic events/high stress/depressive responses or patients who have no specific dysfunctional or stress-related characteristics boost the treatment effect. Patients who happened to receive the fitting personalized treatment showed an almost 2-fold increase in effect size and a 50% reduction in drop-out. In this previous study, we did a post hoc analysis—the aim is now to a priori assign patients based on an optimized treatment algorithm.

#### Ecological momentary low-level diary intervention for activity-based attention modulation (EMDI)

We will use a positive activity diary as a low-level intervention with the goal of diverting the focus of attention away from pain and negative body and emotional experiences. This smartphone-based ecological momentary intervention app will not assess pain, negative mood or stress but the absence of pain, positive mood and positive events as targets for refocusing on positive events rather than pain. This will include enhancing, consolidating and interactive ecological momentary intervention components. In previous studies, we developed and tested a new pain dairy that focuses on pain-free phases and activity rather than pain and disability. We found significantly lower pain and stress and higher mood ratings at the end of a 4-week trial period when the positive activity diary was implemented (Nees et al., submitted). We therefore suggest that implementing this diary as an EMI may be a useful and safe low-level intervention for patients with pain who do not show any significant comorbidity or other psychobiological pathogenetic mechanisms.

### Randomization and allocation

For the allocation of the participants, a computer-generated list of random numbers will be used. Randomization for the pilot study will be carried out by the Interdisciplinary Center for Clinical Trials (IZKS) Mainz using permuted blocks of variable lengths. The randomization lists will be implemented in the electronic case report form system (eCRF) such that randomization can be performed electronically as new participants are added to the study. After providing informed consent and the acquisition of baseline data, participants will be randomly assigned to experimental intervention (personalized allocation) or control intervention (non-personalized allocation) via this eCRF system. Allocation will be managed by an independent study manager involved neither in sequence generation, assessments or treatment. All processes will be monitored and controlled for correctness by the IZKS Mainz. This process will be started only after the enrolled participants will have completed all baseline assessments and it is time to allocate the intervention. Randomization will be stratified by cluster, so that patients have a 50% chance of being allocated to the treatment matching their cluster, and 50% of being allocated to one of the two interventions (25% chance each) not matching their cluster.

### Blinding

Patients, therapists and the researchers carrying out participant assessments will be blinded to the respective condition (personalized vs. non-personalized), and success of blinding will be evaluated to explore possible source of bias. The double-blinding of patients and data collectors (i.e. patients, therapists and psychologists) is kept during the course of the study and statistical analysis will be also done with blinding maintained to avoid bias. Randomization authorities from the Interdisciplinary Center for Clinical Trials (IZKS) Mainz will be instructed to report any suspected breach of the blinding procedures.

### Sample size calculation

The study will be performed in an exploratory fashion and is planned as a pilot study to describe the feasibility and safety of personalized treatments for CMSP as a primary outcome, as well as an initial estimation of signals efficacy and utility as secondary outcomes. Even though a formal power calculation is not necessary in a pilot study, we nevertheless performed a power calculation to better estimate the initial signals of efficacy and utility.

For power considerations, we use a mixed-model with repeated measurements (MMRM), a two-sided significance level of 5% and a sample size of 90 patients (→45 per study arm →90 total from a total of 105 patients at an assumed dropout rate of 15%). The MMRM takes into account also the interim measurements for each patient and allows therefore a fuller use of the data than an ANCOVA. The sample size of 105 patients allows to calculate our feasibility measures with a 95% confidence interval width from 11 to 19% (for varying proportion 0.1–0.5) based on a Wald interval for binary measures [40]. Moreover, patients with data with at least one measurement can be used for the primary analysis; therefore, we expect fewer patients not to be usable for the analysis compared to an ANCOVA. Between repeated measurements, a correlation of 0.3 is assumed. Then, the study has a power of 80% to detect a true effect size of *f* = 0.22, a power of 85% for *f* = 0.23 and 90% power for a true effect size of *f* = 0.25. Dropouts will be analysed according to the underlying reasons for dropout and distinction will be made between those dropouts that are preventable by modification of study design and those that are not preventable by study design adaptations.

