Feasibility objectives will be quantified. If appropriate, 95% confidence intervals will be calculated based on the Wilson Score interval for binary measures. We favoured the Wilson Score interval against Wald interval due to their good properties for small numbers of trials, compared to Wei and Hutson [40]. For the analysis of the primary outcome, we will use the complete and pseudonymized data set and follow the intention-to-treat approach which includes all patients in the group they were allocated to by randomization. This approach preserves the allocation of treatment by randomization and it will be as close as possible to the ITT ideal of including all randomized patients. As sensitivity analysis, the analysis will be repeated in the per-protocol (PP) set, excluding patients with major protocol violations. Additional sensitivity analyses will explore the effects of the treatments the patients actually received. The null-hypothesis H0 (no difference occurs in the population means with regard to pain severity at T1 between the experimental intervention and the control intervention) will be tested against H1 (there is a difference in the population means of pain severity differences between the two groups at T1 and T0). Provided that the model assumptions are fulfilled, the null hypothesis will be tested using a (robust) mixed linear regression model at a significance level of 5%. The primary outcome (pain severity at T1, difference to T0) will be analysed using mixed-effects model repeated measurements after 4, 8 and 12 weeks (=T1). The analysis will be adjusted for condition, gender and baseline (T0) pain severity. Compound symmetry will be assumed. Because of the exploratory nature of the study, the observed initial signals of efficacy and utility will be considered more important than the *p*-values. The corresponding *p*-values of these tests will be interpreted purely descriptively. We will compute effect sizes and interpret them together with the respective 95% confidence intervals. Regarding secondary endpoints, exploratory data analysis will be performed using appropriate analytical methods depending on the respective parameter. Details of the statistical analyses will be fixed in a statistical analysis plan developed by the statistics department of IZKS Mainz prior to database closure. The safety analysis includes calculation and comparison of frequencies and rates of adverse events. Furthermore, statistical methods are used to assess the quality of data and the homogeneity of intervention groups. All analyses will consider gender aspects. Prior to all analyses, we will pre-specify a statistical analysis plan.

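### The stated 80/85/90% power fits an effect averaged over weeks 4, 8 and 12, while the hypothesis is set at T1 (week 12), where the same effect size gives roughly 54–69%

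*Protocol article*

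**What the plan says.** The Sample size calculation section bases its power considerations on a mixed model for repeated measurements, "a two-sided significance level of 5" per cent and "a sample size of 90 patients", 45 per arm ("90 total from a total of 105 patients at an assumed dropout rate of 15" per cent). It credits the model with using the interim measurements. It adds that "Between repeated measurements, a correlation of 0.3 is assumed", and concludes that "the study has a power of 80% to detect a true effect size of" f = 0.22, with 85% for f = 0.23 and 90% for f = 0.25. It does not say which contrast f describes or how many measurements enter the calculation. The Overview section gives the allocation: "All patients eligible will be randomly assigned 1:1 to a personalized or non-personalized treatment arm".

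The Statistical analyses section states the null hypothesis as "no difference occurs in the population means with regard to pain severity at T1" between the two arms. The primary outcome there is pain severity at T1 as a difference to T0. It is analysed with a repeated-measures mixed model at 4, 8 and 12 weeks, week 12 being T1, under compound symmetry. On model terms it says: "The analysis will be adjusted for condition, gender and baseline (T0) pain severity". It leaves further detail to a statistical analysis plan.

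**The concern.** A repeated-measures model can answer two different questions about the arms. One is whether they differ on average over the post-baseline visits. The other is whether they differ at the last visit. Averaging three measurements correlated at 0.3 removes much of the noise, so the first question has far more power than the second for the same per-visit effect. The power section does not say which question its figures answer. The hypothesis names the last visit.

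The two sections fit together only if the treatment difference is fully present at week 4 and stays constant to week 12. The article does not state that assumption. It also plans to examine the endpoints at weeks 4 and 8 for temporal and dose-response patterns (Outcomes section), which suggests that a time course is thought possible.

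At stake is how the pilot is read afterwards. A T1 interval that includes zero could be taken as coming from a study with 80% power at d = 0.44. If the effect grows over therapy, an averaged estimate presented as the T1 effect could also mislead the sizing of the planned multicentre trial.

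**Working it through.** **Inputs.** From the Sample size calculation section: N = 90 (45 per arm), two-sided 5%, correlation ρ = 0.3, f = 0.22/0.23/0.25. From the Statistical analyses section: m = 3 post-baseline visits (weeks 4, 8, 12) and compound symmetry. My readings, not stated in the article: f is the between-arm effect at each visit, so d = 2f with two equal arms (0.44/0.46/0.50); and the baseline–T1 correlation equals the same 0.3.

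**Step 1: reproduce the stated figures.** For the between-arm effect averaged over m visits, the F test has 1 and N − 2 = 88 degrees of freedom and noncentrality

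λ = f² · N · m / (1 + (m − 1)ρ).

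With m = 3 the multiplier is 90 × 3 / 1.6 = 168.75:

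| f | λ | Power | Stated |
|---|---|---|---|
| 0.22 | 0.0484 × 168.75 = 8.17 | 80.7% | 80% |
| 0.23 | 0.0529 × 168.75 = 8.93 | 84.0% | 85% |
| 0.25 | 0.0625 × 168.75 = 10.55 | 89.5% | 90% |

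Solved the other way, 80/85/90% power needs f = 0.218/0.233/0.252, which round to the three published values.

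The alternatives tried do not fit all three figures:

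- m = 1: 54/58/65%
- m = 2: 73/76/83%
- m = 4: 85/88/93%
- m = 5: 88/90/94%
- group-by-time interaction with m = 3: 98/99/99%, or 59/63/71% if the factor m is left out of λ

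The article does not give m in the power section. The simultaneous match makes the three-visit average the evident source.

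**Step 2: power for the T1 contrast.** With arm means free at each visit and complete data, weeks 4 and 8 carry no information on the week-12 difference. A generalised least squares check of that model gives the same values as the single-visit test, with λ = f² · N. With baseline adjustment the residual variance is 1 − 0.3² = 0.91 and λ = f² · N / 0.91, with 87 denominator degrees of freedom.

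| f (d) | λ, unadjusted | Power | λ, baseline-adjusted | Power |
|---|---|---|---|---|
| 0.22 (0.44) | 4.36 | 54.2% | 4.79 | 58.1% |
| 0.23 (0.46) | 4.76 | 57.9% | 5.23 | 61.9% |
| 0.25 (0.50) | 5.63 | 65.0% | 6.18 | 69.1% |

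**Step 3: effect detectable at T1 with 80% power.** f = 0.299 unadjusted (d about 0.60) and f = 0.285 adjusted (d about 0.57), against the stated f = 0.22 (d = 0.44).

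**Step 4: sensitivity.**

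- With 105 randomized and about 15% monotone dropout (an assumed pattern), T1 power is 54.5–65.4% unadjusted and 58.3–69.3% adjusted across the three f values, so using partial data hardly changes the picture.
- An unadjusted change score would give 41.5/44.6/50.9%, but the plan does adjust for baseline.
- As an illustration only, suppose the effect grows linearly to week 12. The visit average is then (1/3 + 2/3 + 1)/3 = 2/3 of the T1 effect. For T1 effects of f = 0.22/0.23/0.25 the averaged test of Step 1 then has λ multiplied by 4/9 and power of 47/50/57%. The article gives no trajectory.

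**The case against.** The strongest reply is that the power is correctly calculated for the model as listed. If condition, gender and baseline are the whole set of terms, the condition coefficient is the average over visits and the stated figures apply to it. They are even conservative, since baseline adjustment would raise them to about 87/90/94%. Under a constant effect from week 4, that coefficient is also the T1 effect. This stands, and it rules out calling the figures an arithmetic error. What it leaves is a hypothesis worded for one visit beside a power statement for the average of three, joined by an assumption that is nowhere stated.

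A reader might go further and treat the lack of a condition-by-visit term as a fault. The document does not support that. The sentence on adjustment may be only a list of covariates, since it omits even visit, and an article may leave such terms to the analysis plan it refers to.

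A reader might also infer that the trial is underpowered for its purpose. That is not supported either. The primary objective is feasibility and safety, the article says a pilot needs no formal power calculation, p-values are to be read descriptively, effect sizes are to be read with confidence intervals, and no feasibility criterion depends on an efficacy test.

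Finally, the T1 figures depend on how f and the baseline correlation are read. That is true, and they should be quoted with those conditions.

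**Conclusion.** The point holds as a mismatch of contrasts. The published power belongs to the difference averaged over weeks 4, 8 and 12, and the published hypothesis is at week 12. For the hypothesis as worded, the same effect sizes have about 54/58/65% power, or 58/62/69% with baseline adjustment. This rests on f being the per-visit effect and, for the adjusted figures, on a baseline–T1 correlation of 0.3. The stated 80/85/90% carries over to T1 only if the effect is constant from week 4.

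Severity is moderate. Sample size, feasibility verdicts and safety reporting are untouched. What is affected is how an inconclusive T1 result is interpreted and what effect is carried into the design of the confirmatory trial.

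**What to change.** Make the power statement and the hypothesis refer to one contrast, in either of two ways.

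(a) Keep T1 as the target. Take the treatment estimate from the week-12 contrast of a model with visit and condition-by-visit terms. Restate the power for that contrast, giving the definition of f and the assumed baseline–T1 correlation. Under the readings used here that is about 58/62/69% for f = 0.22/0.23/0.25, or 80% for d of about 0.57.

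(b) Define the hypothesis as the average between-arm difference over weeks 4–12, and label the present figures as power for that average under an equal effect at each visit. Report the week-12 difference separately with its confidence interval.

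Either way the cost is a few sentences in the sample size and analysis sections, with no change to the number of patients. Under (a) the stated power becomes less favourable. Under (b) the efficacy question is no longer specific to the end of treatment.
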